### 17.4 Analysis Populations

The "all subjects" population includes all subjects who have been enrolled into the study. The "safety population" includes all subjects who have inserted at least one dose of the study gel. The "randomized population" includes all subjects who were randomized to treatment.

### 17.5 Endpoints

#### 17.5.1 Primary

#### **Safety**

- Number and percent of subjects with TEAEs, SAEs, and TEAEs leading to premature discontinuation.
- Number, percent and, in the investigator's judgment, medical significance of abnormalities in physical exams, pelvic exams, and biopsies once product has been administered.
- Number, percent and, in the investigator's judgment, medical significance of abnormalities in clinical laboratory parameters, once product has been administered.

**Pharmacokinetics (PK)**

Evaluation of concentrations of GRFT in blood during and after a single dose of PC-6500 (the initial dose); then during and after 14 days of daily use of PC-6500 vaginal gel, with an estimation of:

- Area under the time-concentration curve ( $AUC_{0-last}$ ;  $AUC_{0-\infty}$ )
- Peak concentration ( $C_{max}$ )
- Trough concentration ( $C_{min}$ )
- Time to blood concentration ( $T_{max}$ )
- Elimination half-life ( $T_{1/2}$ )
- Apparent clearance ( $Cl/F$ )

Details will be elaborated in the SAP.

**17.5.2 Exploratory**

- 1) Post-treatment concentrations of GRFT and CG in CVLs.
- 2) Changes between baseline and after treatment in anti-HIV activity of CVLs in cell-based assays and mucosal explants.
- 3) Changes between baseline and after treatment in transcriptome analysis of gene expression in tissues and in concentrations of immune mediators in CVL.
- 4) Changes between baseline and after treatment in the vaginal microbiome.
- 5) Changes between baseline and after treatment in ADA detection in blood.
- 6) Association between CVL drug levels with anti-HIV activity.
- 7) Changes between baseline and after treatment in anti-*E. coli* activity in CVLs.

**17.6 Safety Analysis**

Safety summaries will be performed on the safety population.

AEs will be coded in accordance with the current version of the Medical Dictionary for Regulatory Activities (MedDRA). Summary of all AEs will be based on TEAEs which include all events that occur on or after the first dosing date and on or before the 7th day after the last dosing date in the OL period of the study and on or before the 14th day after the last dosing date in the randomized period.

The number and percent of the subjects for each AE and SAE will be summarized by system organ class and preferred term for each treatment group.

The summaries of physical exam (including pelvic exam) results will be presented by treatment group for each visit and for the changes from baseline to each visit. Shift tables will be presented to summarize the changes of abnormalities for each parameter.

Changes in vital signs will be summarized for each treatment group.

Clinical laboratory evaluations will be summarized by treatment group for each visit. The abnormalities for each parameter will be summarized for each treatment group. Changes in baseline values and in absolute values for each laboratory parameter will be summarized for each treatment group using shift tables and summary statistics.

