| Laboratory                                                        | Urine  | 
 
• <math>\beta</math>-hCG
 
• Dipstick UA, if indicated
 
• Urine culture, if indicated
 
                                                                                                                                                                                                                                                                                                                                                                                                                                                                                                                                                                                                                                                                                                                                                                                |
|                                                                   | Blood  | 
 
• Baseline PK prior to dosing – record exact time (hours/minutes) of pre-dose blood draw
 
• Pre-dose Hematology, Chemistry and Coagulation (see Section 10.8)
 
                                                                                                                                                                                                                                                                                                                                                                                                                                                                                                                                                                                                                                                                                                               |

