|                                                                           | Blood  | 
 
• Pre-dose hematology, chemistry and coagulation (see Section 10.8)
 
• Pre-dose PK sample before 1st dose
 
• Pre-dose ADA testing
 
                                                                                                                                                                                                                                                                                                                                                                                                                                                                                                                                                                                                                                                                                                                                                                                                                                               |
|                                                                           | Pelvic | 
 
• Vaginal microbiome
 
• CVL (API concentrations, PD, immune mediators, E. coli, RSID)
 
• Vaginal pH, if indicated
 
• Wet mount, if indicated
 
                                                                                                                                                                                                                                                                                                                                                                                                                                                                                                                                                                                                                                                                                                                                                                                                                            |

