### 14.2 Adverse Events Definitions and Reporting Requirements

#### 14.2.1 Definition of Terms

**Adverse Event:** An AE is defined as any untoward medical occurrence associated with the use of a drug in humans, whether or not considered drug related. As such, an AE can be an unfavorable or unintended sign (including an abnormal laboratory finding), symptom or disease temporally associated with the use of investigational product or study participation, whether or not considered related to the product or study participation. In addition to novel events, an AE may be an exacerbation of a pre-existing medical condition that was present prior to study entry. This definition will be applied from the time a potential subject signs the ICF.

**Treatment Emergent Adverse Events (TEAEs)** are defined as any AE that begins on or after the first dose of the study drug and up to seven days after the final study drug dose, or pre-existing conditions that worsened during the same timeframe.

**Non-Treatment Emergent AEs** are defined as those reported between the date the informed consent form was signed and the first dose of study drug, and more than seven days after the last study drug dose.

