#### 14.2.4 Recording Adverse Events

The Investigator is responsible for assessing all AEs that occur at any time during the study. The Investigator must make a determination of relatedness, seriousness, and intensity in the CRFs for each AE.

All AEs will be recorded in the appropriate CRFs. AEs will be recorded using a recognized medical term or diagnosis that accurately reflects the event and includes the following information (when applicable):

- Date condition or event started.
- Date of resolution. If the event has not resolved at the end of the study reporting period, it will be documented as still present or ongoing in the CRFs. However, every effort should be made to obtain the outcome.
- Indication of whether the condition was pre-existing prior to study entry or not, and if yes, whether it has worsened in the severity/intensity or frequency, in which case it is reported as an AE. Conditions present prior to study entry that do not worsen in severity/intensity or frequency are not considered AEs.
- Intensity/Severity: AEs that change in intensity are recorded at the intensity level that is the most severe, as reported by the subject or observed by the Investigator.
- Relationship to investigational product, as evaluated by the Investigator.
- Possible etiologies and whether the event meets criteria as a serious adverse event (SAE) and therefore requires immediate notification to the Sponsor.
- Seriousness: If the event meets 1 or more of the regulatory criteria in the definition of an SAE (see below), the event should be classified as serious. See below for SAEs.

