## 20.3 Risk-Benefit Statement

### 20.3.1 Risks

It is not expected that this trial will expose subjects to unreasonable risk. However, as this is the first time GRFT is being tested in humans, there may be unforeseen risks.

The main risk for subjects in the main study is the pain, discomfort, and possibility of bleeding from the vaginal biopsies (and less so, the cervical biopsies).

In addition, phlebotomy may lead to excessive bleeding, discomfort, feelings of dizziness or faintness, and/or bruising, swelling and/or infection. Pelvic examination may cause mild discomfort and/or embarrassment. Taking of pelvic specimens may cause spotting during or after the pelvic exam. Disclosure of HIV and STI status may cause worry, sadness or depression.

Participation in clinical research includes the risks of loss of confidentiality and discomfort with the personal nature of questions when discussing sexual behaviors. Although the study site will make every effort to protect subject privacy and confidentiality, it is possible that a subject's involvement in the study could become known to others, and that social harms may result. For example, in an effort to comply with local requirements to report communicable diseases including HIV-1, sites may be required to report these diseases to local health authorities.

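### Sections 14.2.1 and 17.6 define treatment-emergent AEs differently, so an AE with onset on Day 1 before the gel is inserted is in under one rule and out under the other

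*Protocol*

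**What the plan says.** Protocol 14.2.1 (Definition of Terms) defines a TEAE as "any AE that begins on or after the first dose of the study drug" and closes the window "up to seven days after the final study drug dose", with no distinction between the two study periods. Worsening of a pre-existing condition in that time also counts. The same section classes as non-treatment-emergent the AEs reported "between the date the informed consent form was signed and the first dose of study drug", and those more than seven days after the last dose.

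Protocol 17.6 (Safety Analysis) bases the summary of all AEs on "TEAEs which include all events that occur on or after the first dosing date". It ends the window on the 7th day after the last dosing date in the open-label (OL) period and on the 14th day after it in the randomized period.

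The number and percent of women with TEAEs is the first primary safety item in the synopsis, 7.6 and 17.5.1. The laboratory item in 17.5.1 is limited to abnormalities after product administration. The same item in the synopsis and in 7.6 has no such limit.

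For AE recording, 14.2.4 lists "Date condition or event started" among the items and lists no clock time of onset.

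**The concern.** A calendar date is a coarser anchor than a dose, and on Day 1 the difference covers a period with many procedures. In both periods women have blood drawn, a pelvic examination, a cervicovaginal lavage and a vaginal swab before the first insertion. Safety laboratory samples are also taken then: "Pre-dose Hematology, Chemistry and Coagulation" at OL Visit 1 (11.2) and "Pre-dose hematology, chemistry and coagulation" at randomized Visit 2 (12.3). Section 20.3.1 expects some effects of these procedures. It names dizziness, bruising and bleeding from phlebotomy, and says of pelvic sampling: "Taking of pelvic specimens may cause spotting during or after the pelvic exam".

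Under 17.6 as worded, such an event counts as treatment emergent although the gel cannot have caused it. The same event one day earlier would not count. With 7 women in an uncontrolled period and at most 14 and 6 in the randomized arms, a single classification decision is visible in the reported percentage. Two programmers working from the same protocol could produce different primary safety tables.

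**Working it through.** The plan has no figure to reproduce: 17.3 says no formal sample size calculation was made, and none bears on this point. The check sets the two rules side by side and then applies simple arithmetic.

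**Step 1. Classify the same event under each rule.**

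| Onset of the AE | 14.2.1 | 17.6 taken literally |
|---|---|---|
| Day before the first dose | not a TEAE | not a TEAE |
| Day 1, before insertion | not a TEAE | TEAE |
| Day 1, after insertion | TEAE | TEAE |
| Randomized period, Days 22 to 28 (14 doses taken) | not a TEAE | TEAE |

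The second and fourth rows disagree.

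**Step 2. Can the second row occur?** Yes. The AE definition in 14.2.1 applies from signature of the consent form, and it allows an abnormal laboratory finding to be an AE. Section 14.2.2 exempts only conditions present before consent that do not deteriorate. A new pre-dose event on Day 1, or a pre-dose laboratory result that the investigator reports as an AE, is therefore recordable. If the woman is then dosed, she is in the safety population (17.4).

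**Step 3. Length of each disagreement.**
- Start: the part of Day 1 before insertion, so less than one day.
- End, randomized period, last dose on Day 14: 14 + 7 = Day 21 under 14.2.1, and 14 + 14 = Day 28 under 17.6. The difference is 7 days, or 7/28 = 25% of the Day 1 to Day 28 window in 17.6.
- End, OL period, single dose on Day 1: 1 + 7 = Day 8 under both. There is no conflict.

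**Step 4. Effect of one reclassified woman who has no other TEAE.** The shift is 100 × 1/n percentage points.
- OL period, n = 7: 100/7 = 14.3 points. The estimate moves from 0/7 (exact 95% interval 0 to 41.0%) to 1/7 (0.4 to 57.9%), taking 0 against 1 case as the example.
- PC-6500, n = 14: 100/14 = 7.1 points.
- Placebo, n = 6: 100/6 = 16.7 points.

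Section 9.4 makes 14 and 6 upper limits and says that enrolling all 20 women will not be feasible. The randomized shifts are therefore at least these values per woman. A woman who has another TEAE anyway adds nothing.

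**Step 5. Number of such women.** The protocol gives no rate for pre-dose Day 1 events, so only the per-woman effect can be stated.

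**The case against.** The strongest reply is that 14.2.1 is the formal definition and 17.6 only paraphrases it. On that view pre-dose events are expressly excluded, and handling of same-day onset is ordinary detail for the SAP, which is not at hand. This holds in part. A reader might infer from 17.6 that the primary endpoint definitely counts pre-dose events. The protocol does not support that, because 14.2.1 says the opposite. But 17.6 is the passage that sets the AE tables, and nothing says which section prevails. A convention in the SAP could reduce the practical effect. It would not remove the contradiction in the protocol.

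Four further inferences go too far:

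- *The baseline laboratory sample becomes a primary outcome.* Section 17.5.1 limits the laboratory endpoint to the time after administration, and 17.6 summarizes laboratory values as changes and shifts from baseline. What remains is the narrower case of a pre-dose result reported as an AE, plus the missing limit in the synopsis and 7.6.
- *The data cannot separate before from after the dose.* Randomized Visit 2 has AE assessments both before and after Dose 1 (12.3). For the OL period, 7.5 and Appendix 1 provide for both. The time of insertion is recorded to the minute (11.2, 12.3). The list in 14.2.4 is not the case report form.
- *The decision to start the randomized period is distorted.* TEAEs are among the items reviewed under 7.7, but the criterion is whether all seven women tolerated the dose, as judged by named medical roles. It sets no TEAE count.
- *A given number of false cases can be expected.* Any such figure would need an assumed rate with no basis in the documents. Some potential cases also drop out: at randomized Visit 2, a condition found at the pre-dose pelvic examination that needs swabs or treatment leads to discontinuation before dosing (12.3). Procedure effects that begin after insertion are TEAEs under both rules.

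Finally, pre-dose events in the randomized period fall on both arms alike. They can raise each arm's percentage but do not systematically favor one arm.

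**Conclusion.** The point holds as an internal contradiction, not as a settled rule that pre-dose events are counted. Sections 14.2.1 and 17.6 classify an AE with onset on Day 1 before insertion in opposite ways, and the first primary safety endpoint depends on that classification. Applied literally, 17.6 counts events that the gel cannot have caused.

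The per-woman sizes in the working assume that she has no other TEAE and, for the randomized arms, that enrollment is full. The total effect is unknown and may be nil. The OL percentage is the more exposed result, because no control group there shows the procedural background.

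On duration, the larger conflict between the same two sections is at the other end of the window: seven days in the randomized period against less than one day at the start. Both should be settled together.

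**What to change.** 1. Keep one TEAE definition and refer to it everywhere. In 17.6, start the window at the first dose, as 14.2.1 does, instead of at the first dosing date.
2. For AEs dated on the first dosing day, record whether onset was before or after Dose 1. The separate pre-dose and post-dose AE assessments and the recorded insertion time already supply the information.
3. In the synopsis and 7.6, give the laboratory item the same post-administration limit that it has in 17.5.1.
4. In the same edit, choose one end for the randomized-period window and use it in both sections. AE reporting already runs to 14 days after the final dose in that period (14.2.3), so data collection allows either end.

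The cost is one sentence in 17.6, a matching edit to the window end, a short phrase in two endpoint lists, and one tick box on the AE form if it does not already have one. No visit, sample or assessment is added.

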## 17.7 Statistical Analysis of PK Measurements

If absorption is observed, then PK analysis will be performed. The aim of the PK analysis for this study is to gather exploratory information on absorption, distribution and elimination (not to compare bioavailability using multiple formulations or doses). Drug concentrations and drug exposure will be determined using blood samples for GRFT concentrations.

Blood concentrations of GRFT will be assessed at multiple time points during the trial. In the OL period, sampling will occur before dosing and at 0.5, 1, 2, 3, 4, 6, 8, 10, 12 and 24h after the single dose. In the randomized portion, sampling will occur before dosing on Days 1, 3, 5, 8, 11 and 14; on Day 1 at 4h or 8h post-dose, according to the randomization scheme; on Day 14 at 0.5, 1, 2, 3, 4, 6, 8h post-dose; and on Day 15, 24h post-dose 14. If absorption occurs,  $C_{max}$ ,  $C_{min}$ ,  $T_{max}$ ,  $T_{1/2}$ , apparent clearance (Cl/F),  $AUC_{0-last}$ , and  $AUC_{0-\infty}$  after dosing through the end of the elimination period will be computed as the data allow. For all PK concentrations and computed PK parameters, the number of observations, means, standard deviations, medians, first and third quartiles, and ranges will be presented.

## 17.8 Statistical Analysis of Exploratory Endpoints

Concentrations of GRFT and CG in CVLs will be measured for each subject before and after the first dose. All subjects in the OL period will have CVLs collected 24h post-dose. In the main study, one-half of subjects will be randomized to CVL specimen collection at 4h after the first dose (n=10) and the other half will be randomized to CVL specimen collection 8h after the first dose (n=10). Mean concentration, minimum and maximum will be calculated and concentrations will be summarized for subjects sampled at the three different time points.

Log-normal generalized linear mixed models will be used to analyze changes between baseline and post-gel use in anti-HIV activity of CVL in explants and in concentrations of immune mediators in CVL.

Anti-HIV activity in CVL will be also assessed using a TZM-bl assay with the HIV-1ADA-M laboratory strain. Assays will be performed on serial dilutions to establish a dose-response curve. GraphPad Prism software will be used to prepare curve-fitting analysis and to calculate the median cytotoxicity concentration ( $CC_{50}$ ) and the half-maximal effective concentration values ( $EC_{50}$ , based on CVL dilution or drug concentrations) for all CVLs. Correlations between levels of GRFT in CVL and its anti-HIV activity will be calculated.

Transcriptome will be analyzed using Deseq2 and Voom software to evaluate statistical significance of changes in gene expression in tissue between baseline and post gel application.

Vaginal swabs will be collected to determine potential changes in microbiome post-gel exposure relative to pre-exposure. The unique fraction metric (UniFrac) will be used to measure the differences between microbial communities using the phylogenetic information. Linear discriminant analysis Effect Size (LEfSe) will be employed to compare the microbiome communities before and after gel application.

ADA will be assessed qualitatively both in baseline serum samples and in serum samples collected after daily GRFT use (Day 14), one week after the last gel application (Day 21) and two weeks after the last gel application (Day 28). Shift tables will be presented by treatment arm to summarize changes in detection of ADA between baseline and Days 14, 21 and 28.

Mean E. coli inhibitory activity of CVL samples collected at baseline and at different time points after gel application will be calculated. Comparisons of the inhibitory activity of CVLs collected at different time points after gel application and versus CVL collected at baseline will be performed by paired t-tests or Wilcoxon-signed rank tests.

For all the computed PD parameters, number of observations, means, standard deviations, medians, and ranges will be presented by treatment arm and specimen collection time point.

RSID testing of CVLs or vaginal swabs will be done to determine if unprotected (condomless) sex occurred because semen could have an impact on some exploratory analyses. Specimens that test positive may be eliminated from some of the final analyses, to be further described in the SAP.

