### 10.9.2 CVL and swab: drug concentrations, PD, immune mediators, anti-*E. coli* activity, and vaginal microbiome

CVLs will be collected to determine (1) GRFT and CG concentrations; (2) anti-HIV activity in cell-based assays and mucosal explants; (3) concentrations of genital tract immune mediators; (4) anti-*E. coli* activity; and (5) RSID testing to determine if condom-less sex occurred (NOTE: in the randomized portion of the study, the first RSID test will be done at enrollment using a swab instead of CVL). Each subject in the OL period will have 1 CVL collected at baseline (enrollment, before dosing) and 24h post-dose. Each subject in the randomized period will have 1 CVL collected at Visit 2/Day 1 before the first dose, after the first dose (at 4 or 8h, depending on stratification) and after the 14th dose (Day 15). Vaginal swabs will be collected from all subjects at before the first dose and following the last dose (Day 2 in the OL period; Day 15 in the randomized period) to determine if there are changes in the vaginal microbiome after GRFT administration.

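### Section 17.8 names LEfSe, whose rank screen is unpaired, to compare matched before/after vaginal swabs; this costs power to detect within-woman microbiome change

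*Protocol*

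**What the plan says.** Protocol Section 10.9.2 sets the sampling: "Vaginal swabs will be collected from all subjects at before the first dose and following the last dose". The last-dose swab falls on Day 2 in the open-label period and Day 15 in the randomized period. The purpose given there is "to determine if there are changes in the vaginal microbiome after GRFT administration". Section 17.5.2 lists the endpoint as "Changes between baseline and after treatment in the vaginal microbiome".

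Section 17.8 restates the aim, "Vaginal swabs will be collected to determine potential changes in microbiome post-gel exposure relative to pre-exposure", and names two tools. The first is a distance: "The unique fraction metric (UniFrac) will be used to measure the differences between microbial communities using the phylogenetic information". The second is the before/after comparison itself: "Linear discriminant analysis Effect Size (LEfSe) will be employed to compare the microbiome communities before and after gel application". No pairing, blocking or subject term is attached to either.

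The same section does use within-subject methods for some other repeated samples. For anti-E. coli activity, comparisons "versus CVL collected at baseline will be performed by paired t-tests or Wilcoxon-signed rank tests". For explant activity and immune mediators, "Log-normal generalized linear mixed models will be used to analyze changes between baseline and post-gel use".

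**The concern.** The data are matched pairs and the question is whether a woman's own community changes. LEfSe, with before and after as its two classes, screens each taxon with the Kruskal-Wallis rank test. The Protocol does not spell this out; it is a property of the method it names. That test compares two sets of swabs as though they came from different women. Stable differences between women, which cancel when each woman is compared with herself, stay in its error term.

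At stake is sensitivity. In a first-in-human study of a vaginal product, an undetected shift in the vaginal flora could be reported as no effect. The study is small: at most 14 women receive active gel for 14 days, and Section 9.4 says that enrolling all 20 randomized women will not be feasible. There is little power to give away.

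**Working it through.** **Inputs from the Protocol.** Two swabs per woman (10.9.2); 7 open-label women and up to 20 randomized, of whom up to 14 active (Synopsis, 9.4, 17.3). Section 17.3 says no formal sample size calculation was made, so there is no power figure to reproduce.

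**Assumptions not in the Protocol.** Two-sided 5% per taxon; bivariate normal before/after values with within-woman correlation rho from 0 to 0.7; shifts of 0.5 or 0.8 between-woman SD.

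**Mechanism, using means in place of ranks.** With SD 1, the mean change has true standard error √(2(1−rho)/n), but an unpaired test assumes √(2/n). At n=14:
- The unpaired test rejects only if the mean change exceeds 1.96 × √(2/14) = 0.741.
- At rho 0.5 the true standard error is √(1/14) = 0.267. For a true shift of 0.5, unpaired power is about Φ((0.5 − 0.741)/0.267) = Φ(−0.90) = 18%. Paired power is about Φ(0.5/0.267 − 1.96) = Φ(−0.09) = 46%, a large-sample figure that overstates what a small-sample test attains.
- With no shift, the unpaired test rejects with probability 2 × Φ(−0.741/0.267) = 0.6%, well below 5%.

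**Simulation of the rank tests** (Kruskal-Wallis against exact Wilcoxon signed-rank, n=14, at least 20,000 data sets per setting, no multiplicity adjustment):

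| rho | No shift | 0.5 SD | 0.8 SD |
|---|---|---|---|
| 0 | 5% vs 5% | 24% vs 23% | 51% vs 48% |
| 0.3 | 2% vs 5% | 20% vs 30% | 51% vs 63% |
| 0.5 | 0.9% vs 5% | 18% vs 40% | 52% vs 78% |
| 0.7 | 0.2% vs 5% | 14% vs 59% | 54% vs 94% |

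**A constructed case.** Baselines are 1, 2, …, 14 and every woman rises by 1.5. Among the 196 before/after pairings, the after value is the larger in (2 + 3 + … + 14) + 14 = 118, against 98 expected. The variance is 14 × 14 × 29/12 = 473.7, so z = 20/21.76 = 0.92 and p = 0.36. All 14 changes have the same sign, so the sign test gives 2/2¹⁴ = 0.0001.

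**With false discovery control.** Benjamini-Hochberg at 5% was applied to both tests (assumed 20 independent taxa, 2 of them shifted, n=14):
- 0.5 SD: about 1% vs 7% (rho 0.5) and under 1% vs 16% (rho 0.7).
- 0.8 SD: about 8% vs 31% (rho 0.5) and 5% vs 58% (rho 0.7).

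**Open-label group, n=7.** The smallest exact two-sided signed-rank p-value is 2/2⁷ = 0.0156. Benjamini-Hochberg at 5% can then declare a taxon only if at least 0.0156/0.05 = 31% of all taxa sit at that minimum, which is 7 of 20. In the simulation (2 of 20 shifted, up to 0.8 SD) the paired test found nothing and the unpaired screen less than 1%.

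**The case against.** **Detail belongs in the SAP.** Section 17.1 defers details to a SAP that is not shown, and 17.8 gives LEfSe no class definition, significance level or threshold. A SAP could add pairing. This stands for UniFrac: it is named only as a distance, a within-woman permutation test is not excluded, and its absence is no finding. It does not rescue LEfSe, which the Protocol fixes as the before/after comparison and whose screen has no subject term.

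**The correlation is assumed.** The two randomized-period swabs are about two weeks apart and at different cycle days, and the Protocol gives no information on stability. This stands. At rho 0.3 the loss is about 10 points for 0.5 SD, and at zero there is none. The simulation also uses normal data and covers only the rank screen, not LEfSe's effect-size step.

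**Readings that go too far.**
- A reader might infer spurious findings. The table shows the reverse: the screen rejects too rarely when nothing changes.
- A reader might infer that the microbiome is the only endpoint in 17.8 without pairing. It is not: the paired biopsies go to DESeq2 and Voom, also with no subject term stated, although those tools can take one.
- A reader might infer that a paired test would show an effect of GRFT. No before/after test can. That needs the contrast with PC-535, which 17.8 does not state for the microbiome.
- A reader might take the unadjusted powers as what the fix delivers. With false discovery control they are much lower.

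**Conclusion.** The method named for the before/after microbiome comparison does not fit the matched design. The consequence is lost power when a woman's two swabs are positively correlated. Per taxon, unadjusted, at n=14 and a 0.5 SD shift, the loss is about 10 percentage points at rho 0.3, 22 at rho 0.5 and 45 at rho 0.7, and almost nothing at rho 0. Adjusted for false discoveries, both tests are weaker but the paired one stays ahead at n=14. At n=7 taxon-level testing has essentially no power either way.

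Fourteen is the active-arm maximum, so actual power will be lower if fewer are enrolled. The endpoint is exploratory, and the primary safety and PK conclusions do not depend on it. The documents do not support reading this as a threat to those conclusions. It is worth correcting because a paired analysis suits the stated question and costs almost nothing.

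**What to change.** In Section 17.8:
- Replace LEfSe as the before/after test with a within-woman analysis per taxon: a Wilcoxon signed-rank test on each woman's change in log-ratio abundance, or a mixed model with woman as random effect. Control the false discovery rate across taxa.
- Compare the within-woman change between PC-6500 and PC-535 before attributing any shift to GRFT. With at most 14 and 6 women this contrast will be imprecise, so give estimates with intervals.
- Report the open-label microbiome results descriptively.
- Keep LEfSe, if wanted, as a descriptive display.

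The cost is a wording change and a small change to the analysis code, including a stated rule for zero counts in the log-ratios. No new samples or visits are needed. The drawback is less direct comparability with publications that used LEfSe.
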